### Sample-size considerations

This is a pilot trial and therefore a formal power calculation is not required. However, providing data for the power calculation of a definitive trial is an important function of a pilot study, and a minimum number of 30 participants per group is recommended to estimate a parameter for this purpose [47]. We therefore aim to screen 2,742 women to arrive at a sample of 60 providing data at the 6-month follow-up. This is based on an estimate from the UK Infant Feeding Survey 2005 [7] that 220 (8%) of those screened will screen positive. We expect 10% of these to be ineligible because of substance use [48] and 20% because of other exclusion criteria, leaving 70% (154) eligible for the study. We estimate, based on rates in a comparable study in the US [26], that 78% (n = 120) of this remainder will consent to enter the pilot RCT, with 60 participants in each of the intervention and control arms. This should provide data from at least 30 women in each group at follow-up, allowing for 33% attrition in the first wave [47] and 25% in the second wave (Figure 1). In this way, screening and intervention sample sizes will be sufficient to estimate the actual recruitment and retention rates for a UK sample of pregnant women recruited in antenatal care and provide data on the acceptability of study processes and outcome measures [47].

**Figure 1 F1:**
[figure not shown]
**Flow diagram for the pilot study.** Based on previous data [7], we expect **(A)** 8% to screen positive [7]; **(B)** 10% to be ineligible because of substance use [47] and 20% to be ineligible because of other exclusion criteria. In addition, we expect, based on a comparable US study [26] , **(C)** a 22% refusal rate [27] and **(D)** a 33% attrition rate at first follow-up [46]. At second follow-up we conservatively estimate **(E)** a 25% attrition rate.

Feasibility criteria are recommended for pilot study design [49]. Support for continuing to a main trial will constitute either: 1) recruitment rate of 78% of those eligible, and retention of 67% and 75% of participants at the two follow-up stages respectively; or 2) a finding that, although not achieved in the pilot phase, these rates would be likely to be achieved with feasible modifications to the trial materials or procedures.

### Planned analysis

As this study is a pilot study, no formal hypothesis will be tested. The aim of the study is to provide robust estimates of the likely rates of recruitment, consent, and retention, and also estimates of the variability of the primary and secondary outcomes to help power calculations for a subsequent full-scale RCT.

The summaries of all baseline characteristics will be presented by treatment group. The summary statistics will be computed for all primary and secondary outcome variables. For all continuous variables, the mean, standard deviation, median, and range will be computed for both the intervention and control groups. For categorical variables, the frequencies and proportions will be calculated. The proportion and the 95% confidence intervals will be presented for the estimates of response, positive screening and eligibility rates, and recruitment and retention rates.

Although the study is not powered, the effect of brief intervention will be analyzed using basic exploratory analysis to compare the intervention and control group using the *t*-test and χ^2^ tests. The outcome analysis will also include the computation of economic analysis in the pilot trial, which will allow the assessment of effectiveness and cost-effectiveness in a full trial. The estimates of the outcome variables of this trial will be used for calculation of the sample size for the full trial. SPSS software (IBM version 17.00; SPSS Inc., Chicago, IL, USA) [50] will be used for all the statistical analyses.

Other aspects of trial design will be confirmed based on the acceptability of the study processes and outcome measures to the pregnant women and the midwives responsible for their care.

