New guidance from the Medical Research Council on developing and evaluating complex interventions [29] is intended to help institute appropriate methods in such research and to enhance the usefulness of its evidence. The guidance points out the potential for evaluations of complex interventions such as brief interventions to be undermined by problems that could be highlighted in a pilot study. Piloting is therefore recommended, but should not be used to test a hypothesis [30]. The pilot study should establish the acceptability of procedures, identify likely recruitment and retention rates, and inform a sample-size calculation for a definitive trial [29]. Because brief interventions to reduce alcohol consumption have not been tested previously in UK antenatal care, a pilot study for such research is proposed on this basis.

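### The intervention effect is to be examined only by t-tests and chi-square tests, which fit poorly with the plan's estimation aim, give no interval and ignore randomization by midwife

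*Protocol article*

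**What the plan says.** Two statements in the protocol article point away from testing. The Background, in describing guidance on complex interventions, says: "Piloting is therefore recommended, but should not be used to test a hypothesis". The Planned analysis section begins "As this study is a pilot study, no formal hypothesis will be tested" and then gives the aim as estimating rates and the variability of outcomes for a later power calculation. The Design section keeps the effectiveness hypothesis for the definitive trial.

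The third paragraph of Planned analysis then reads: "Although the study is not powered, the effect of brief intervention will be analyzed using basic exploratory analysis to compare the intervention and control group", and it names the method: "using the *t*-test and χ^2^ tests". The same section promises 95% confidence intervals for response, positive screening, eligibility, recruitment and retention rates. It promises none for the difference between arms.

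The Design and Randomization sections make the midwife the unit of randomization, and Setting gives 31 midwives. Under Sample-size considerations the plan states "This is a pilot trial and therefore a formal power calculation is not required". The criteria for continuing, at the end of that section, concern recruitment and retention only.

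**The concern.** The t-test and the chi-square test are hypothesis tests. Applied to the effect of brief intervention, they address the question that the Design section reserves for the later trial, in a study whose declared purpose is to estimate rates and variability. They are also the only inferential method named for that effect. The quantity that a pilot can usefully report, a difference with its uncertainty, is not specified, while the p-value is.

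There is a technical fault as well. In their standard form both tests assume that women are independent. Here whole midwife caseloads are allocated together, so if outcomes within a caseload are correlated, the standard errors come out too small and the p-values too low.

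What is at stake is how the result is read. With samples of this size, a non-significant result is likely even if a moderate effect exists, and a reader may take it as evidence against the intervention. A chance significant result may be taken as evidence for it.

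**Working it through.** **1. Numbers expected at follow-up (Sample-size considerations).** The plan's aim is "We therefore aim to screen 2,742 women to arrive at a sample of 60 providing data at the 6-month follow-up", starting from "220 (8%) of those screened will screen positive".

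- Positive screens: 2,742 × 0.08 = 219.4 (plan: 220)
- Eligible: 220 × 0.70 = 154
- Consenting: 154 × 0.78 = 120.1 (plan: 120, or 60 per arm)
- First follow-up, third trimester: 60 × 0.67 = 40.2 per arm
- Second follow-up, post-partum: 40.2 × 0.75 = 30.2 per arm, or 60.3 in all (plan: 60)

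The plan's figures reproduce. Both time points matter. The proposed main-trial primary outcome is measured during pregnancy, where about 40 per arm are expected; about 30 per arm remain post-partum.

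**2. What the t-test could show.** The document gives no significance level, effect size or standard deviation. Assume a two-sided 5% level, effects in SD units and, for this step, no clustering. Power comes from the noncentral t distribution with 2n − 2 degrees of freedom and noncentrality d√(n/2).

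| Difference d (SD) | Power, 40 per arm | Power, 30 per arm |
|---|---|---|
| 0.2 | 14% | 12% |
| 0.3 | 26% | 21% |
| 0.5 | 60% | 48% |

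The normal approximation gives 61% and 49% in the last row. By the same approximation, the difference detectable with 80% power is (1.96 + 0.84) × √(2/n): 0.63 SD at n = 40 and 0.72 SD at n = 30. For a binary outcome with assumed proportions of 50% and 65%, power is 27% and 21%.

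**3. What an interval would show.** The 95% half-width is t(0.975, 2n − 2) × √(2/n).

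- n = 40: 1.991 × 0.2236 = 0.45 SD
- n = 30: 2.002 × 0.2582 = 0.52 SD

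**4. Effect of ignoring midwives.** Assume that all 31 midwives contribute equally and that the intracluster correlation (ICC) lies between 0.01 and 0.20; the document gives no ICC. Mean cluster size m is 80/31 = 2.58 at first follow-up and 60/31 = 1.94 at second. The design effect is DE = 1 + (m − 1) × ICC. The true error rate of a nominal 5% test is 2 × [1 − Φ(1.96/√DE)].

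| m | ICC | DE | True type I error |
|---|---|---|---|
| 1.94 | 0.01 | 1.009 | 5.1% |
| 1.94 | 0.05 | 1.047 | 5.5% |
| 1.94 | 0.20 | 1.187 | 7.2% |
| 2.58 | 0.01 | 1.016 | 5.2% |
| 2.58 | 0.05 | 1.079 | 5.9% |
| 2.58 | 0.20 | 1.316 | 8.8% |

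The corresponding half-widths are those of step 3 multiplied by √DE. At the upper ICC of 0.20 this gives 0.445 × √1.316 = 0.51 SD at 40 per arm and 0.517 × √1.187 = 0.56 SD at 30 per arm.

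**The case against.** The protocol does not hide what it is doing. Its denial is limited to a *formal* hypothesis, the comparison is called exploratory, and its sentence opens by conceding that the study is unpowered. The statement in the Background reports guidance and is not an analysis rule. A fair reading is that no confirmatory test is planned and that the arm comparisons are descriptive extras. This stands, and it makes the conflict one between aim and method, not a flat contradiction between two binding rules.

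A reader might also infer that the tests could decide whether the definitive trial goes ahead. The document does not support that: the continuation criteria are 78% recruitment and 67% and 75% retention, or a finding that modifications could achieve them. No efficacy result enters.

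A reader might go further and call the p-values uninterpretable. That is too strong. With about two women per midwife the inflation is mild, and low power makes a null result uninformative without making it meaningless.

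Finally, an interval shows whether zero is excluded, so replacing a p-value with an interval does not stop someone from reading significance into it. That is true, but the interval also shows how wide a range of effects remains compatible with the data, which the p-value does not.

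The labels leave three things unanswered: the method does not serve the stated aim, no interval for the effect is planned, and the named tests ignore the unit of randomization.

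**Conclusion.** The point holds in a limited form. The planned tests sit badly with an estimation aim and, as named, are weak and mildly anti-conservative. Power for half a standard deviation is about 60% in the third trimester and 48% post-partum. True type I error is about 5.1% to 8.8% at a nominal 5%.

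These figures rest on assumptions that the document does not supply: a two-sided 5% level, effects in SD units, an ICC of 0.01 to 0.20, and equal contributions from all 31 midwives. If fewer midwives recruit, or their numbers are uneven, the inflation would be larger than shown.

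The consequence is the risk of misreading an exploratory result. The decision to proceed is not affected. The correction is worth making because it is cheap and the tests serve none of the pilot's stated objectives.

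**What to change.** In Planned analysis, replace the sentence on t-tests and chi-square tests. State that outcomes will be summarized by arm and that the between-arm difference will be given with a 95% confidence interval that allows for clustering by midwife, as exploratory estimation without significance tests. A mixed model, generalized estimating equations with a small-sample correction, or an analysis of midwife-level summaries would each serve. With 31 midwives, and so 15 or 16 per arm under 1:1 allocation, the small-sample correction matters.

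The change needs no extra data and no change to recruitment. It costs a slightly more complex analysis than a simple two-sample test and somewhat wider intervals: at the upper assumed ICC, about 0.51 instead of 0.45 SD at 40 per arm, and 0.56 instead of 0.52 SD at 30 per arm, before any small-sample correction.

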## Methods/Design

### Setting

The trial setting is that of community antenatal care. Under National Health Service (NHS) antenatal care in the UK [31], women initially receive advice from a general practitioner (GP) or midwife about lifestyle, folic-acid supplements, food hygiene, and antenatal screening. A booking appointment subsequently takes place during the first trimester at the woman’s home or in a clinic at the GP surgery. At this meeting, the community midwife provides more detailed information on fetal development, procedures, and resources; carries out assessments to develop an individual care plan; and offers lifestyle advice, screening tests, and an ultrasound scan (carried out at 18 to 20 weeks if desired). Appointments then take place every 2 to 3 weeks from week 25 of pregnancy, in which the midwife carries out routine tests and offers staged advice as appropriate.

For this study, midwives (n = 31) working from four bases of a community midwifery service are recruiting patients over an 8-month period from January 2012. Between them, these midwives provide antenatal care for 36 general practices in Newcastle upon Tyne in north-east England (population 2,607,000; annual live births 30,826), a geographical area with high rates of alcohol misuse and a culture of heavy drinking [32-34]. The practices comprise 41 branch surgeries with diverse patient profiles (total list size 282,034). Each practice is served by one to three midwives and midwives may routinely provide care to patients at one to three practices, depending on practice list sizes and whether or not the midwife works full-time.

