### Randomization

In anticipation of the main trial employing a cluster randomized design to avoid contamination, the unit of randomization is the midwife. It is not practical for individual midwives to deliver both control and intervention conditions in this trial, as training to deliver structured advice will compromise their ability to deliver treatment as usual. Because community midwives may serve multiple GP practices, each midwife consistently delivers either intervention or treatment as usual.

Before screening of women for the trial, midwives were randomized in a 1:1 ratio to either control or intervention group with no concealment of allocation. They were notified of their allocation and trained in the appropriate procedures.

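### Midwives are randomized, but the named tests treat women as independent, and no intracluster correlation is among the planned inputs to the definitive sample size

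*Protocol article*

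**What the plan says.** On design, the Randomization section of the protocol article says: "In anticipation of the main trial employing a cluster randomized design to avoid contamination, the unit of randomization is the midwife". The Setting section gives "midwives (n = 31) working from four bases of a community midwifery service", and Randomization adds that "midwives were randomized in a 1:1 ratio to either control or intervention group". According to the Design, Screening and Consent sections, each midwife screens, takes consent from and advises the women at her own booking appointments.

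On analysis, the Planned analysis section opens with "As this study is a pilot study, no formal hypothesis will be tested". It then says that "the effect of brief intervention will be analyzed using basic exploratory analysis to compare the intervention and control group using the" t-test and chi-squared tests. It promises 95% confidence intervals for the screening, eligibility, recruitment and retention proportions, without naming a method. It lists means, standard deviations, medians and ranges as the outcome summaries and states: "The estimates of the outcome variables of this trial will be used for calculation of the sample size for the full trial". The article nowhere mentions an ICC, a design effect, midwife-level variance or variation in cluster size.

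**The concern.** Women seen by the same midwife share her way of asking about alcohol, her consent conversation, her advice and her practice population. Their outcomes are likely to be positively correlated. With allocation by midwife, the information about the arm difference comes from 31 clusters and not only from the count of women. An ordinary t-test or chi-squared test ignores this and understates the standard error whenever the ICC is above zero.

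Two uses of the pilot are affected. The first is how well its own comparisons and intervals describe uncertainty. The second is the handover to the definitive trial, which is a declared purpose of the pilot. A cluster trial cannot be sized from a standard deviation and participation rates alone; it also needs an ICC and a cluster size.

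**Working it through.** **Inputs from the protocol.** 31 midwives (Setting). From Sample-size considerations: 2,742 screened, 8% positive, 70% of those eligible, 78% of those consenting, then 33% and 25% attrition. No ICC is given, so every ICC below is an assumption.

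**The plan's own cascade.**
- 2,742 × 0.08 = 219.4 (stated as 220)
- 220 × 0.70 = 154
- 154 × 0.78 = 120.1 (120)
- 120 × 0.67 = 80.4
- 80.4 × 0.75 = 60.3 (60)

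The stated figures reproduce. The cascade contains no clustering term.

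**Confidence intervals for rates.** With m = n/31 women per midwife, the design effect is DE = 1 + (m − 1) × ICC. The 95% half-width is 1.96 × √(p(1 − p)/n), multiplied by √DE if clustering is allowed for. For the screen-positive rate:
- Unadjusted: 1.96 × √(0.08 × 0.92/2,742) = 1.02 points.
- At ICC 0.05: m = 88.45, DE = 1 + 87.45 × 0.05 = 5.37, and 1.02 × √5.37 = 2.35 points.

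Half-widths in percentage points:

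| Rate | n | m | Unadjusted | ICC 0.01 | ICC 0.05 | ICC 0.10 |
|---|---|---|---|---|---|---|
| Screen-positive, 8% | 2,742 | 88.5 | 1.0 | 1.4 | 2.4 | 3.2 |
| Eligible, 70% | 220 | 7.1 | 6.1 | 6.2 | 6.9 | 7.7 |
| Recruited, 78% | 154 | 5.0 | 6.5 | 6.7 | 7.2 | 7.7 |
| First retention, 67% | 120 | 3.9 | 8.4 | 8.5 | 9.0 | 9.5 |
| Second retention, 75% | 80 | 2.6 | 9.5 | 9.6 | 9.9 | 10.2 |

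**The named tests.** The true type I error of a nominal 5% test that ignores clustering is about 2 × (1 − Φ(1.96/√DE)). With unequal cluster sizes, DE = 1 + ((1 + CV²) × m − 1) × ICC. A CV of 0.6 is assumed; uneven workloads are plausible because midwives serve one to three practices and some may not work full-time (Setting).

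| Women | ICC | Equal clusters | CV 0.6 |
|---|---|---|---|
| 60 | 0.05 | 5.5% | 6.0% |
| 60 | 0.10 | 6.1% | 6.9% |
| 80 | 0.05 | 5.9% | 6.5% |
| 80 | 0.10 | 6.9% | 8.0% |
| 120 | 0.05 | 6.7% | 7.5% |
| 120 | 0.10 | 8.4% | 10.1% |

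Simulations of the t-test with 80 women and 31 midwives gave 6.5% to 7.3% at ICC 0.05 and 7.4% to 9.9% at ICC 0.10. The higher values arose when the realized cluster sizes varied more than the nominal CV of 0.6.

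**The definitive trial, illustrated.** Assume 20 women per midwife.
- ICC 0.02: DE = 1 + 19 × 0.02 = 1.38. A sample size without it is 1 − 1/1.38 = 28% short.
- ICC 0.05: DE = 1 + 19 × 0.05 = 1.95. The shortfall is 1 − 1/1.95 = 49%.

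With an assumed standardized effect of 0.3 and 80% power, 175 women per arm without clustering become 242 (ICC 0.02) or 342 (ICC 0.05). Recruiting only 175 would leave about 67% or 52% power.

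**The case against.** The strongest defence is that this is a pilot. The comparison is declared exploratory and unpowered, and the progression rule in the Figure 1 section rests on point estimates of recruitment and retention, so no p-value or interval enters it. That stands, and it limits the severity. It does not make a test that ignores the randomized unit suitable for the comparison: being exploratory excuses low power, not a wrong standard error.

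Three stronger readings are tempting and go too far.
- A reader might infer that all the confidence intervals treat women as independent. The article names no method for them, and a condensed article may leave that to a fuller document. Only the t-test and chi-squared tests are fixed in the text.
- A reader might infer that the full trial will be undersized. No definitive sample size exists yet, the article already expects a cluster design, and an ICC could be taken from elsewhere. The shortfall is conditional.
- A reader might see a flat contradiction between testing no formal hypothesis and naming two tests, or an error in not adjusting for the baseline drinking diary. The first is a tension in wording, since the tests are labelled exploratory. The second is a missed gain in precision.

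It is also fair to say that the pilot's ICC will be poor: with 80 women and a true ICC of 0.05, simulated estimates ranged from −0.17 to 0.29 (95% range). That argues for planning over a range of ICCs, not for leaving clustering out.

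**Conclusion.** The point holds in a limited form, as something that should be fixed. The named arm comparisons do not match randomization by midwife, and the listed inputs to the definitive sample size lack those that a cluster trial needs.

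The tests are anti-conservative if the ICC exceeds zero, with a type I error of roughly 5.5% to 10% at assumed ICCs of 0.05 to 0.10, depending on the number of women and the spread of cluster sizes. The effect on the intervals applies only if they are computed without clustering. It is then clear for the screen-positive rate, where each midwife contributes about 88 women, and modest for recruitment and retention, where she contributes about three to five. The 28% to 49% shortfall in a full trial applies only if that trial is sized from the standard deviation alone, at the assumed 20 women per midwife and ICC 0.02 to 0.05.

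**What to change.** In the planned analysis:
- Replace the t-test and chi-squared tests with a model that has midwife as a random effect, or with an analysis of midwife-level summaries (31 − 2 = 29 degrees of freedom). Report arm differences with 95% confidence intervals.
- State that the intervals for the screen-positive, eligibility, recruitment, delivery and retention rates allow for clustering by midwife.
- Report the mean cluster size, its CV, and the ICC with its confidence interval.
- State that the definitive sample size will include a design effect over a stated range of ICCs, because the pilot's own estimate will be imprecise.

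Adjusting the drinking outcomes for the baseline diary value is optional and may gain precision.

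The cost is some extra analysis work and slightly wider intervals. No new data are needed, provided that midwife identity is kept in the dataset.

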### Measures

#### Baseline

The primary outcomes for this feasibility study are rates of eligibility, recruitment, intervention delivery, and participant retention at follow-up. Eligibility will be established by midwives using a checklist of inclusion and exclusion criteria and the AUDIT-C. Rates of recruitment, intervention delivery, and retention will be determined from case report forms. The alcohol counselor will record whether the alcohol intervention was delivered with the participant.

The trial will also measure the proposed outcomes for a future main trial, allowing us to test the usefulness of measures, obtain an estimate of variability to inform power calculations, and assess the acceptability of trial documents. The primary outcome in a full trial will be the maximum number of standard drinks (units) per drinking occasion during the pregnancy, a continuous measure), with secondary outcomes including alcohol abstinence (binary) in the third trimester and 6 months post-partum. Participants will be asked to complete a questionnaire containing three baseline measures, with their midwife’s assistance if requested.

1 The Timeline Follow-Back (TLFB) questionnaire [39] measures alcohol consumption during pregnancy for two weekly periods. The respondent is asked to complete a simple diary (with visual cues) detailing alcohol use in the preceding week. The preceding week might not be typical (for example, a patient might have reduced their drinking as the booking appointment approached), and there may be a tendency to enhance social desirability in responses. Thus, a second diary is requested covering the heaviest drinking week since becoming pregnant. The TLFB has been used as an outcome measure with pregnant women [23,24,40] previously. Scores from the 7-day version, which we will use to minimize the burden on patients, have been found to be strongly correlated with those gathered within longer timeframes [41-43].

2 The AUDIT-C is completed in respect of the participant’s drinking in the 6 months before pregnancy, because the quantity and pattern of previous drinking is predictive of whether or not pregnant women drink during pregnancy [44]. In a full trial, this information will establish whether effects of the intervention differed according to the level of pre-pregnancy drinking.

3 The EuroQoL EQ-5D-3 L instrument measuring quality of life will be completed as part of the health-economics analysis (see below).

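### The exploratory arm comparison and the SD summary leave out the baseline drinking diary, so the effect estimate is less precise than the collected data allow and the definitive sample-size inputs are incomplete

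*Protocol article*

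**What the plan says.** **Comparison of arms.** Under Planned analysis, the protocol article first states that "As this study is a pilot study, no formal hypothesis will be tested". It then adds that "the effect of brief intervention will be analyzed using basic exploratory analysis to compare the intervention and control group", naming the t-test and χ² tests. No covariate is mentioned.

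**Variability.** The same section says: "For all continuous variables, the mean, standard deviation, median, and range will be computed for both the intervention and control groups". It goes on: "The estimates of the outcome variables of this trial will be used for calculation of the sample size for the full trial". The Baseline section under Measures gives as one reason for measuring the proposed outcomes to "obtain an estimate of variability to inform power calculations".

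**Baseline data.** Two 7-day TLFB diaries are requested. For the first, "The respondent is asked to complete a simple diary (with visual cues) detailing alcohol use in the preceding week"; in addition, "a second diary is requested covering the heaviest drinking week since becoming pregnant". AUDIT-C for the six months before pregnancy is also taken, on the ground that earlier drinking predicts whether women drink in pregnancy. The Follow-up section repeats the 7-day TLFB in the third trimester and six months after the due date.

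**Intended definitive outcome.** "The primary outcome in a full trial will be the maximum number of standard drinks (units) per drinking occasion during the pregnancy", described as continuous.

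**The concern.** A baseline version of the outcome can be derived from data the trial already collects, and the protocol itself treats earlier drinking as prognostic. Leaving it out of the comparison has two costs.

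The first is precision: whatever part of the follow-up variation the baseline explains stays in the error term.

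The second is imbalance. According to the Randomization, Screening and Consent sections, 31 midwives were randomized without concealment and told their arm before screening began. They then screen the women and take consent. Few clusters and informed recruiters leave room for both chance and selective differences in baseline drinking, and an unadjusted difference in means carries these into the estimate.

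For the definitive trial, a sample size that takes credit for baseline adjustment needs the baseline/follow-up correlation or the residual SD. The article commits to neither, although supplying inputs for that calculation is one of the pilot's stated purposes.

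**Working it through.** **1. The plan's own figures** (Sample-size considerations). 2,742 × 0.08 = 219.4 (stated 220); 220 × 0.70 = 154; 154 × 0.78 = 120.1 (stated 120); 120 × 0.67 × 0.75 = 60.3, about 30 per arm. The chain reproduces. The article gives no effect size, SD, correlation, alpha or power for the definitive trial.

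**2. Assumptions for the rest.** Baseline/follow-up correlation r = 0.3, 0.5 or 0.7; two-sided alpha 0.05; for the definitive illustration, a standardised effect d = 0.3 and 80% or 90% power. Clustering is ignored on both sides of each comparison.

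**3. Variance after adjustment.** Residual variance = (1 − r²) × raw variance; residual SD = √(1 − r²) × raw SD.

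**4. Pilot precision at n = 30 per arm, in raw-SD units.** The t-test 95% half-width is t(0.975; 58) × √(2/30) = 0.517. The adjusted half-width is t(0.975; 57) × √(2/30) × √(1 − r²) × √(1 + 1/56), where the last term allows for estimating the slope.

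**5. Definitive n per arm, before any design effect.** n = 2(z₀.₉₇₅ + z_power)² × (1 − r²) / d², with r = 0 for the raw SD.

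| | Raw SD | r = 0.3 | r = 0.5 | r = 0.7 |
|---|---|---|---|---|
| Variance factor | 1 | 0.91 | 0.75 | 0.51 |
| Residual SD factor | 1 | 0.954 | 0.866 | 0.714 |
| Half-width, 30 per arm | 0.517 | 0.498 | 0.452 | 0.373 |
| Reduction in width | – | 4% | 13% | 28% |
| n per arm, 80% power | 175 | 159 | 131 | 89 |
| n per arm, 90% power | 234 | 213 | 176 | 120 |

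**6. Direction of any sizing error.** A trial of 175 per arm, sized on the raw SD for 80% power but analysed with adjustment, has power of about 84%, 90% or 98% at the three correlations. It is too large, not underpowered.

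**7. What oversizing would cost in screening.** The plan screens 2,742 / 120 = 22.85 women per woman enrolled. At 80% power the saving over both arms is 2 × (175 − 159) = 32, 2 × (175 − 131) = 88 or 2 × (175 − 89) = 172 women. That is roughly 731, 2,011 or 3,930 fewer to screen, before attrition and design effect.

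**8. Exposure to chance imbalance.** With 30 per arm the baseline difference has a standard error of √(2/30) = 0.258 SD. An imbalance of that size shifts the expected unadjusted follow-up difference by r × 0.258 = 0.077, 0.129 or 0.181 SD with no treatment effect at all.

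**9. How well the pilot can estimate these inputs.** With 60 women (58 degrees of freedom) the 95% limits for the SD are about 0.85 to 1.22 times the estimate. For an observed r of 0.5, Fisher's transformation gives 0.549 ± 1.96/√57, that is 0.28 to 0.67, and so a variance factor between 0.92 and 0.55. The correlation is worth reporting, but with its interval.

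**The case against.** **A reader might infer that the definitive trial will be sized on the wrong SD.** The document does not support that. It fixes the definitive hypothesis and primary outcome but no analysis model. The raw SD is the right input for an unadjusted analysis and a conservative one for an adjusted analysis (step 6). Nor is information lost: the diaries are held, and the correlation can be computed when the definitive trial is designed.

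**The comparison decides nothing.** It is labelled exploratory and not powered. The pilot's primary outcomes are rates of eligibility, recruitment, intervention delivery and retention, and the progression criteria concern recruitment and retention only. This stands and limits the importance of the point. It does not remove it, because variability estimates for the power calculation are a stated aim.

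**A condensed article may leave covariates to a fuller document.** This is fair as to silence on detail. But the article positively names the tests and the summary statistics, and these are what is questioned.

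**The correlation is unknown.** This stands. The remark about prediction concerns drinking before pregnancy and whether women drink at all, not a first-trimester diary against later maximum units. The article also warns that the preceding week may be atypical. At r = 0.3 the gain is small.

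**Adjustment is not a cure for selection.** This stands too. It deals with imbalance in the measured covariate only. The baseline questionnaire may be completed with help from a midwife who knows the allocation, so the covariate itself may be affected.

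**A reader might also assume complete baseline diaries.** The article says only that women are asked to complete them and that midwives prompt for missing items.

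**Conclusion.** The point holds as an inexpensive improvement, not as an error in the pilot's design. The named comparison is valid as an exploratory summary but uses less than the collected data offer and is more exposed to baseline imbalance in drinking. The gain rests on an assumed correlation: a 9%, 25% or 49% cut in variance at r = 0.3, 0.5 or 0.7, before clustering. The consequence for the definitive trial is possible oversizing, and only if that trial is analysed with baseline adjustment but sized on the raw SD. The feasibility rates and the criteria for proceeding are untouched.

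**What to change.** In Planned analysis, for continuous drinking outcomes, replace or supplement the t-test with a linear model of follow-up units on arm and the matching baseline value, allowing for clustering by midwife. State how the baseline is derived from the diaries; for maximum units per occasion, the largest single-occasion figure in the heaviest-week diary is one candidate.

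Report the baseline/follow-up correlation, with its confidence interval, and the residual SD beside the raw SD. Say that the definitive sample size will use whichever matches the analysis chosen for that trial.

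An adjusted model for abstinence is optional: with about 60 women under 31 midwives, roughly two per cluster, it may be unstable. Note in the text that adjustment does not correct for unmeasured selection under unconcealed allocation.

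The cost is a change of analysis wording and a few extra lines of output. No new data are needed, and the named software can fit the model.
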